### Recruitment {15}

One hundred participants will be recruited from the University of Siegen via internal mailing lists for students. After participants have contacted us via email for study participation, details on the study will be given in a short telephone interview and the aforementioned eligibility criteria will be checked.

### Assignment of interventions: allocation

#### Sequence generation {16a}

Participants will be randomly assigned to the VR group or the active control group according to an externally constructed, randomization plan with a 1:1 ratio. A computerized simple randomization will be implemented based on computer-generated random numbers to control for the equal size of the study groups.

#### Concealment mechanism {16b}

The randomization plan will be password-protected, and the password is only known to the lead investigator and the recruiters. The lead investigator will keep a separate list of the generated randomization plan to guarantee unbiased allocation.

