#### Implementation {16c}

Separate individuals will be responsible for randomization, allocation, and data acquisition to avoid potential bias. The lead investigator who will not be involved in participant recruitment and data acquisition will generate the randomization plan. The recruiters of the trial management group will allocate included participants sequentially based on the randomization plan. The experimenters of the trial management group will conduct data acquisition.

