### Assignment of interventions: blinding

#### Who will be blinded {17a}

Since participants will be blinded until the onset of the relaxation phase, baseline and stress phases will not be influenced by group assignment. Blinding participants for the relaxation phase will not be possible since either the VR or an own relaxation method will be applied. Similarly, blinding is not possible for the experimenters. The data analysis will comprise two separate processing stages: analysis of raw data in Matlab 2020b (The Mathworks Inc., Natick, MA, USA) and statistical tests in SPSS Statistics 27 (Armonk, NY: IBM Corp.). Missing values and outliers will be treated at the first analysis stage. The data analyst will be blinded until the performance of the statistical test at the second analysis stage.

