#### Procedure for unblinding if needed {17b}

Participants will be unblinded immediately before the relaxation phase by revealing their allocation and giving the respective instructions. The data analyst will be unblinded at the second analysis stage.

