### Oversight and monitoring

#### Composition of the coordinating center and trial steering committee {5d}

The steering committee consisting of all lead and principal investigators of the two universities as well as the industrial cooperation partners will have monthly, virtual meetings to address goals and progress of the overall multidisciplinary project “NOSTRESS.” Public involvement will be realized in the form of public, interactive virtual meetings with external experts to discuss issues of stress, health, and technology organized by one of the cooperation partners. The lead investigator of the present RCT trial (subproject of “NOSTRESS”) was responsible for the study design, prepared the protocol, and will organize bi-weekly virtual meetings with the trial management group. In this bi-weekly meetings, the trial management group will report on problems and progress of ongoing data collection. The trial management group will consist of seven research assistants: three of them will be responsible for participant recruitment and screening (referred to as recruiters), and four will conduct the laboratory testing sessions (referred to as experimenters). A technical support team consisting of two experienced post-doctoral researchers will assist in the occurrence of technical problems and participate in the bi-weekly meetings, whenever necessary. The lead investigator will prepare the randomization plan and will monitor the acquired data for completeness and validity (e.g., corrupt recordings). The lead investigator together with the principal investigator will decide on trial termination and will write up study results for publication.

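### The recruiters who screen and allocate can open the randomisation list, so upcoming allocations are not concealed from the people deciding on inclusion

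*Protocol article*

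**What the plan says.** All references are to the protocol article.

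- **Access to the list.** Concealment mechanism {16b}: "The randomization plan will be password-protected, and the password is only known to the lead investigator and the recruiters".
- **Safeguard offered.** Same section: "The lead investigator will keep a separate list of the generated randomization plan to guarantee unbiased allocation".
- **Who the recruiters are.** The section on the coordinating center and steering committee {5d} describes seven research assistants, of whom "three of them will be responsible for participant recruitment and screening (referred to as recruiters".
- **How screening is done.** Recruitment {15}: after a candidate makes contact, "details on the study will be given in a short telephone interview and the aforementioned eligibility criteria will be checked".
- **Who allocates.** Implementation {16c}: "The recruiters of the trial management group will allocate included participants sequentially based on the randomization plan".
- **Separation of roles.** Same section: "Separate individuals will be responsible for randomization, allocation, and data acquisition to avoid potential bias". The lead investigator, who generates the plan, takes no part in recruitment or testing.
- **When participants learn their arm.** Procedure for unblinding {17b}: "Participants will be unblinded immediately before the relaxation phase by revealing their allocation and giving the respective instructions".

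**The concern.** Concealment means that the person who decides whether and when a candidate enters the trial cannot know which arm comes next. Here that person can open the list. Eligibility is settled in a telephone conversation, and one criterion (a past trauma that the stress pictures might reactivate) calls for judgement. Scheduling also leaves room to bring one person forward or put another back. If those choices are made with the next arm in view, even without intent, the two groups can differ before any treatment is given.

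The stakes are higher than usual in this design. The primary outcomes are self-rated stress and relaxation, and from the relaxation phase onwards the participant knows the arm. Blinding cannot protect those ratings, so the comparison leans heavily on groups that were formed without foreknowledge.

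**Working it through.** No formula in the plan bears on this point, and the sample size is not affected by it. The check is to follow one candidate through the stated roles.

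1. **Sequence.** Sequence generation {16a} and Implementation {16c}: the plan is computer-generated in advance, 1:1, by the lead investigator. A complete list therefore exists before candidates are screened.
2. **Screening and inclusion.** Recruitment {15} and the committee section {5d}: the three recruiters screen, with the eligibility check made by telephone.
3. **Allocation.** Implementation {16c}: the recruiters assign included participants in list order.
4. **Access.** Concealment mechanism {16b}: the recruiters know the password to the plan. No entry-by-entry release, central service or sealed envelope is described.

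Steps 2, 3 and 4 name the same group. At the moment of inclusion or scheduling, the next arm is therefore knowable to those acting.

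**What the access changes.** With the list open, the next arm can be known with certainty (probability 1). Without it, under 1:1 simple randomisation, a guess is right with probability 1/2. The difference between 1 and 1/2 measures predictability, not bias.

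**What each safeguard covers.**

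| Safeguard | What it does | Does it hide the next arm from recruiters? |
|---|---|---|
| Password {16b} | Keeps out anyone who is not given it | No, they have it |
| Separate list held by the lead investigator {16b} | Lets out-of-order or altered assignments be found later | No |
| Separate individuals {16c} | Divides randomisation, allocation and data acquisition | No, screening is not in that division |
| Participants blinded until relaxation {17a} | Protects ratings before relaxation from the participant's own knowledge | No, it acts after inclusion |
| Analyst blinded until the statistical test {17a} | Protects data cleaning | No, it acts after inclusion |

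A recruiter who follows the list order exactly, but chooses whom to place at the next position, leaves no discrepancy between the two copies. The duplicate list therefore cannot support the claim made for it in {16b}.

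**Timing.** Table 1 places consent before allocation and allocation before the first assessment. The Procedure section {11a} has written consent given at the start of the laboratory session. The article thus leaves unclear when, relative to written consent, an arm is attached to a person. The arm is not disclosed to the participant until just before relaxation {17b}, so the article shows no reason why the recruiters should know it earlier.

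**The case against.** The strongest defence has four parts.

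- **Little to select on.** The telephone check covers age, illness, medication and trauma. The planned scales for stress, rumination, mindfulness and self-efficacy are filled in later. Recruiters have no planned measure of how readily someone relaxes, so deliberate steering would be crude. This stands and limits how large a bias is plausible. It does not restore concealment, because conversation, the trauma judgement and scheduling still leave room for choice.
- **Departures can be found.** The duplicate list does allow this. It stands as an audit trail, not as concealment.
- **Access may be narrower than it looks.** The article does not say in so many words that recruiters see every entry at once. But a password to the plan gives access to the plan, and no staged release is described.
- **Recruitment is over.** This stands, and it changes the remedy for completed sessions to reporting.

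Three stronger readings are tempting and should not be adopted.

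- A reader might infer that Implementation {16c} contradicts itself. It does not: it separates randomisation, allocation and data acquisition, and never promises to separate screening from allocation.
- A reader might infer that experimenters know the arm during baseline and stress, which would undercut the statement that "baseline and stress phases will not be influenced by group assignment". The sentence on experimenters in {17a} directly follows one limited to the relaxation phase and may share that limit. The list password is not given to experimenters, and no section says that they know the arm earlier.
- A reader might put a figure on the bias, for example in standard deviations against the margin. The only margin stated is 25% on a success proportion, and nothing in the article gives the share of candidates who could be steered or how they would differ. Any such figure would be invented.

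**Conclusion.** The point holds. As written, allocation is not concealed from the recruiters, who screen, schedule and assign, and the statement in {16b} that the duplicate list secures unbiased allocation is not supported. This rests on one assumption: that knowing the password means being able to read upcoming entries, which is the plain reading.

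Selection bias is possible, not demonstrated. Nothing shows that any recruiter looked ahead or acted on it. Neither the size nor the direction of a bias can be derived from the documents. The defect lies in the mechanism and in the assurance given about it.

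**What to change.** **For any session still to be run.** Withdraw the recruiters' access to the list. The lead investigator, already outside recruitment and testing, can continue to generate it. Release one assignment at a time, only after eligibility, written consent and inclusion have been recorded, through sequentially numbered opaque sealed envelopes or the session software (Presentation is already in use). The best moment is the one {17b} already names, just before relaxation. Recruiters then never see the sequence, and whoever runs the session cannot know the arm during baseline and stress, which also removes the ambiguity in {17a}.

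*Cost:* a short script or a set of envelopes, and VR equipment ready at every session, with the room set up alike in both arms until the reveal. No extra staff are needed.

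**For sessions already run.**

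1. Replace the statement on unbiased allocation in {16b} with what the separate list can do, which is to allow departures from the sequence to be detected.
2. Disclose in the report that the recruiters could open the list, or describe any staged release that was in fact used, and name this as a limitation if it applies.
3. Report candidates screened but not enrolled, with reasons and, where an arm had been attached or the next list position can be reconstructed, by that arm.
4. Report baseline and pre-relaxation values by arm, and the result of comparing actual assignments with the lead investigator's list.

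*Cost:* wording and two tables. Similar values before relaxation would be reassuring but would not prove that no selection took place, and the report should say so.

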#### Implementation {16c}

Separate individuals will be responsible for randomization, allocation, and data acquisition to avoid potential bias. The lead investigator who will not be involved in participant recruitment and data acquisition will generate the randomization plan. The recruiters of the trial management group will allocate included participants sequentially based on the randomization plan. The experimenters of the trial management group will conduct data acquisition.

### Assignment of interventions: blinding

#### Who will be blinded {17a}

Since participants will be blinded until the onset of the relaxation phase, baseline and stress phases will not be influenced by group assignment. Blinding participants for the relaxation phase will not be possible since either the VR or an own relaxation method will be applied. Similarly, blinding is not possible for the experimenters. The data analysis will comprise two separate processing stages: analysis of raw data in Matlab 2020b (The Mathworks Inc., Natick, MA, USA) and statistical tests in SPSS Statistics 27 (Armonk, NY: IBM Corp.). Missing values and outliers will be treated at the first analysis stage. The data analyst will be blinded until the performance of the statistical test at the second analysis stage.

#### Procedure for unblinding if needed {17b}

Participants will be unblinded immediately before the relaxation phase by revealing their allocation and giving the respective instructions. The data analyst will be unblinded at the second analysis stage.

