### Statistical methods

#### Statistical methods for primary and secondary outcomes {20a}

Analysis of acquired raw data will be conducted in Matlab 2020b (the Mathworks Inc., Natick, MA, USA). All physiological data will be visually screened. ECG data will be analyzed with the Pan-Tompkins algorithm for QRS detection [38, 39]. Heart rate will be estimated as the number of beats per minute. Heart rate variability will be estimated using root mean square of successive differences (RMSSD, [40]). The tonic skin conductance level and the number of non-specific phasic skin conductance responses will be estimated using the matlab toolbox Ledalab [41]. Respiratory rate will be estimated per minute using a custom-made matlab script that band pass filters the data to frequencies of 0.05 to 1 Hz before detection of inhalation peaks and exhalation troughs. SPSS Statistics 27 for Windows (Armonk, NY: IBM Corp.) will be used for statistical analyses. To test the effects of time (within-subject factor), group (between-subject factor), and the time by group interaction, repeated measures ANOVAs will be performed. Additional two sample *t* tests will evaluate the group differences at relaxation and post-relaxation.

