#### Interim analyses {21b}

Study data will be analyzed by the lead investigator in the middle (interim analysis at *N* = 50) and after completion of data acquisition. Planned analyses are described in SPIRIT item 20a. There will be no formal stopping rules since we do not anticipate problems detrimental to participants. Data collection will be stopped when at least fifty participants will be included in each group (VR, active control). The lead investigator and the principal investigator will make the final decision to terminate the data collection.

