#### Methods for additional analyses (e.g., subgroup analyses) {20b}

To explore if the current stress level, trait mindfulness, and trait self-efficacy impact the success of the applied relaxation method, we will include them as covariates in the above models. No additional subgroup or adjusted analyses are planned.

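### The analyst's blind ends at statistical testing, already at the N = 50 interim, and the person named as analyst holds the randomization list; coded arms under a separate key-holder would secure it

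*Protocol article*

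**What the plan says.** Analysis has two stages: raw-data processing in Matlab, then statistical tests in SPSS. Who will be blinded {17a} says: "The data analyst will be blinded until the performance of the statistical test at the second analysis stage". It places data cleaning in the blinded stage: "Missing values and outliers will be treated at the first analysis stage". Procedure for unblinding {17b} confirms the end point: "The data analyst will be unblinded at the second analysis stage". Neither section says why the tests need the arms to be known, and neither mentions coded arms.

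For the second stage, Statistical methods {20a} says "repeated measures ANOVAs will be performed" for time, group and their interaction, and adds: "Additional two sample *t* tests will evaluate the group differences at relaxation and post-relaxation". For current stress level, trait mindfulness and trait self-efficacy, {20b} says "we will include them as covariates in the above models".

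Interim analyses {21b} says who analyses and when: "Study data will be analyzed by the lead investigator in the middle (interim analysis at *N* = 50) and after completion of data acquisition". For content it points back: "Planned analyses are described in SPIRIT item 20a". Under Implementation {16c} the lead investigator generates the randomization plan. Under Concealment mechanism {16b} the lead investigator keeps a separate list of it and shares its password with the recruiters.

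**The concern.** Analyst blinding is one of few protections left in this trial. Participants know their arm from the relaxation phase on, experimenters know it, the primary outcomes are self-reported, and there is no independent data monitoring committee. The investigators' department also helped to develop the VR.

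Three features of the plan weaken that protection.

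- The blind ends when testing starts, although the tests do not require it. Some discretion remains at that point: two primary ratings at ten times with no stated ranking, how the ANOVAs and t tests are specified, and the covariate models.
- The interim brings this forward. Once the planned tests have been run at N = 50, the analyst knows the arms and the interim direction of effect while half of the data are still to be cleaned.
- The person named as analyst holds the key to the allocation throughout.

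At stake is whether cleaning and modelling choices can be shown to have been made without knowledge of the arm.

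**Working it through.** **1. Does coding affect the design figures?** Inputs from Sample size {14}: 80% success in both groups, margin 25%, power 90%, alpha 0.05. Per arm, n = (z_alpha + z_power)² × [p(1−p) + p(1−p)] / margin² = (1.645 + 1.282)² × 0.32 / 0.0625 ≈ 43.9, so 44 per arm and 88 in total. This reproduces the stated 88 with a one-sided alpha of 0.05 (one-sided 0.025 would give 54 per arm, 108 in total). Arm identity does not enter the formula, so coding changes neither 88 nor the target of 100.

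**2. Do the planned tests need arm identity?** The t statistic is (mean A − mean B)/SE, so swapping labels reverses only its sign. The ANOVA sums of squares add squared deviations over both groups, so they do not change at all. A check on simulated data (50 per arm, four time points for the ANOVA) agrees; the values illustrate symmetry and say nothing about this trial.

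| Quantity | A/B | Labels swapped |
|---|---|---|
| F, group | 5.099 | 5.099 |
| F, group × time | 0.797 | 0.797 |
| t | 0.437 | −0.437 |
| two-sided p | 0.663 | 0.663 |
| 95% CI of difference | −0.532 to 0.832 | −0.832 to 0.532 |
| one-sided non-inferiority p, assumed margin of 1 point | 0.0006 | 0.0076 |

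Only the last row depends on which code is VR. Both directions can be computed under codes, and the applicable one read off after decoding.

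**3. Order of events under the plan.**

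- At N = 50, {21b} calls for the analyses of {20a}. These include the group comparisons, so the second stage is reached.
- Under {17a} and {17b} the analyst is unblinded at that point.
- 100 − 50 = 50 participants still have to pass through first-stage handling of missing values and outliers.
- No step re-establishes the blind for them.

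**4. Who holds the key.** {21b} names the lead investigator as the person who analyses; {16b} and {16c} give the same role the plan and the list. An A/B label attached to existing participant IDs could be decoded from that list. Sequence generation {16a} calls the plan externally constructed, which fits poorly with {16c}, but {16b} gives the lead investigator access on either reading.

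**5. Which files can be masked.** The VAS ratings of stress and relaxation are collected in the same form in both arms (2 + 3 + 2 + 2 + 1 = 10 times). Other files can give the arm away: sense of presence in the VR, the strategies reported after the relaxation phase, possibly the adherence questionnaire, and respiration, which only the VR slows by a guided pattern.

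**The case against.** {17a} and {17b} agree with each other, and unblinding an analyst at the testing stage is neither an error nor a contradiction. The steps most open to bias, missing values and outliers, are assigned to the blinded stage. {20a} names the models and the t-test time points, {20b} names the covariates and rules out further subgroup or adjusted analyses, and a separate analysis plan may fix the rest. Recruitment ended in May 2021, so if the interim ran as planned, that analyst's blind cannot be restored.

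Much of this stands. A reader might infer that imputation is done with arms known; {17a} puts missing values in the first stage, so that holds only through the interim, for the second half. A reader might also infer that the analyst is unblinded because the tests require it; the article gives the timing and no reason. Nor would relabelling the arms be sufficient and free, because the analyst could decode the labels and some self-reports reveal the arm.

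Two further limits apply. {17a} does not name the data analyst, so the overlap with the lead investigator rests on {21b}, and first-stage processing may be done by someone else. And the interim itself discloses the allocation of the first 50 only; for the second 50 it would be known through an arm code in the files or the retained list.

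The objection does not answer the order of events: with the planned tests run at N = 50, the blind promised for data cleaning is not assured for the second half.

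**Conclusion.** The point holds as a minor, specific weakness. The plan ends the analyst's blind at a step that does not require it. Through the interim it leaves data cleaning for 50 of 100 participants without an assured blind, and it gives the list to the person named as analyst. This rests on two readings: that the analyst in {17a} is the lead investigator of {21b}, and that the interim includes the group comparisons of {20a}.

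No bias or error-rate inflation can be put in figures from the document. Inflation calculated for choosing among several tests would measure multiplicity, not the effect of knowing the arm. Nor does the article show that any choice was made with the arm in view; it shows only that the plan does not prevent it.

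**What to change.** Amend {17a} and {17b}, and align {16b}, {16c} and {21b} with them:

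1. Arms stay coded A and B, with participant IDs re-coded, through the interim and final tests of the VAS ratings and of the questionnaires that do not reveal the arm.
2. An existing team member who does not analyse the data holds the key. Whoever runs the tests has no access to the randomization list or its password, which excludes the lead investigator and the recruiters as the roles now stand.
3. Presence, strategy and adherence self-reports and the physiological files, respiration above all, are withheld and analysed afterwards.
4. Confidence intervals or non-inferiority results are computed in both directions. The code is broken only after the final output is dated and locked.
5. If the interim was already run with arms known, say so, and give cleaning of the second half and the final tests to someone who saw neither the interim results by arm nor the list.

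Cost: a small change of roles, a re-coding step and a dated output file. Sample size, alpha and power do not change.
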